### Randomization and Blinding

After obtaining the baseline mobile screen time data, participants were randomly assigned to 1 of 3 groups in a 1:2:2 (control vs self-selected vs assigned) ratio. This assignment was carried out using a stratified randomized permuted block design with a block size of 5 using the *ralloc* command on Stata 17 software (StataCrop LLC). The allocation was stratified based on 2 variables: status in the institute (employee or student) and the quartile of baseline average mobile screen time. Following randomization, the research team became aware of the allocation groups. Blinding at the participant level was not possible due to the nature of the intervention. Participants were informed about their group before the start of the intervention period. They were not told about other groups or the groups of other participants. The CONSORT (Consolidated Standards of Reporting Trials) flow diagram for the study is provided in Figure 1.

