### Sample Size

The target sample was 300 participants, assuming a conservative effect size (*d*) of 0.12 for the difference between self-selected and assigned conditions and 0.15 for the difference between the intervention group and control conditions, with 80% power and an α of .05. The effect size was estimated based on past studies in this domain [22,23].

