#### Group Allocation

The 1-week period after the baseline was the group allocation period. During this period, the 156 participants who shared their mobile screen data were randomly assigned to 1 of 3 study groups. Initially, participants in the self-selected group were given information regarding their baseline average daily mobile screen time and asked to choose a target for reducing their mobile screen time based on this average. After the participants in the self-selected group had made their specific target choices, an email was sent to participants in the assigned group informing them about their given target.

All participants, including the control groups, received an email about the benefits of reducing mobile screen time and their baseline average daily mobile screen time.

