### Statistical Analysis

We will estimate the effects of mobile screen time, target achievement rate, GAD-7, PHQ-9, and daily mood scores by comparing variables of interest between the intervention and baseline and between the postintervention and baseline periods. To perform this analysis, we will use Stata 17 and R (version 4.2.2; Free Open-Source Software). The unadjusted effects will be calculated as differences in the means and conducting a 2-tailed Student *t* test for significance. For adjusted effects, we will use simple ordinary least square regression adjusting for participant-level covariates: age, gender, and employee or student. We assume errors to be correlated within each participant but uncorrelated across participants. A separate equation will be used for each dependent variable. The regression equations are provided in Multimedia Appendix 1. For mobile screen time, we will estimate a difference-in-difference ordinary least square regression. To account for the impact of the intervention and the postintervention period, we will incorporate dummy variables for the period. Specifically, assessing the effect on mobile screen time and target achievement rate postintervention will provide valuable insights into habit formation. Multilevel or hierarchical linear modeling will also be used to allow differential relationships between mood and screen time at the individual level.

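### The Student t test named for the unadjusted effects can be miscalibrated for contrasts with the smaller control arm; a Welch test avoids this at almost no cost

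*Protocol article*

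**What the plan says.** Under Statistical Analysis, the article fixes the unadjusted method: "The unadjusted effects will be calculated as differences in the means and conducting a 2-tailed Student" t test. It names Stata 17 and R as software and gives no variance option. The opening sentence of that section describes the effects as "comparing variables of interest between the intervention and baseline and between the postintervention and baseline periods".

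The between-arm contrasts appear elsewhere. The objectives ask for the effect of incentives and targets, and for self-selected against assigned targets. Sample Size assumes an effect size "of 0.12 for the difference between self-selected and assigned conditions" and "0.15 for the difference between the intervention group and control conditions".

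Randomization and Blinding sets a "1:2:2 (control vs self-selected vs assigned) ratio", and Group Allocation reports that "the 156 participants who shared their mobile screen data were randomly assigned".

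Adjusted effects come from ordinary least squares regression with errors correlated within participant, and screen time from a difference-in-difference regression. The equations are in Multimedia Appendix 1, which is not shown.

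**The concern.** The two-sample Student t test, as the name is ordinarily used, pools the two variances. With equal groups this does little harm when the variances differ. With unequal groups the pooled variance is dominated by the larger group, while the uncertainty of the difference comes mostly from the smaller one. If control is the more variable group, the standard error is too small and the interval too narrow. If the intervention arms are more variable, the standard error is too large and power is lost, in a trial whose Limitations section already concedes that power may be low.

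Unequal variances are plausible here. Targets are percentage cuts from each person's own baseline, so an effect proportional to baseline would compress screen-time levels in the paid arms. The Discussion also expects some participants to miss the average target and others to meet it, and such a mixed response could widen the spread. The direction cannot be known in advance, which favours a test that holds either way.

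**Working it through.** The article gives no error rate and no SD for this test, so there is no stated figure to reproduce.

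**Group sizes.** From 156 randomized at 1:2:2:
- control: 156/5 = 31.2
- each intervention arm: 2 × 31.2 = 62.4
- both intervention arms: 4 × 31.2 = 124.8

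Arm counts are not stated in the text, so 31, 62 and 125 are derived values.

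**SD ratio (assumption).** Let k = control SD / intervention SD. Take a uniform 20% cut in the paid arms, with equal SDs (set to 1) at baseline and at untreated follow-up.
- Raw follow-up level: the paid SD becomes 0.8, so k = 1/0.8 = 1.25.
- Change from baseline, with baseline/follow-up correlation r (assumed, as none is given): control variance = 2(1 − r); paid variance = 1 + 0.64 − 1.6r.
  - r = 0.5: 1.00 and 0.84, k = 1.09
  - r = 0.7: 0.60 and 0.52, k = 1.07
  - r = 0.8: 0.40 and 0.36, k = 1.05
  - r = 0.9: 0.20 and 0.20, k = 1.00
  - r = 0.95: 0.10 and 0.12, k = 0.91

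**Error rate of the pooled test.** Set the control variance to 1 and the intervention variance to v = 1/k².
- Pooled variance: s² = [(n₁ − 1)v + (n₂ − 1)] / (n₁ + n₂ − 2)
- Variance the test uses: E = s²(1/n₁ + 1/n₂)
- True variance: T = v/n₁ + 1/n₂
- The critical value acts as if it were t₀.₉₇₅ × √(E/T).

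For n₁ = 125 and n₂ = 31, df = 154 and t₀.₉₇₅ = 1.975.

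| k | v | s² | E | T | √(E/T) | effective critical value | two-sided rate |
|---|---|---|---|---|---|---|---|
| 1.25 | 0.64 | 0.710 | 0.02859 | 0.03738 | 0.875 | 1.728 | 8.6% |
| 1.07 | 0.867 | 0.893 | 0.03594 | 0.03919 | 0.958 | 1.892 | 6.0% |
| 1.00 | 1 | 1 | 0.04026 | 0.04026 | 1 | 1.975 | 5.0% |
| 0.80 | 1.5625 | 1.453 | 0.05849 | 0.04476 | 1.143 | 2.258 | 2.5% |

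Simulation with normal data (400,000 null replicates per point) agrees: 8.65% at k = 1.25 and 2.52% at k = 0.8. Across the change-score correlations above, the formula gives 6.3%, 6.0%, 5.8%, 5.0% and 3.8%.

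**One arm against control (62 v 31).** Simulated: 6.9% at k = 1.25 and 3.5% at k = 0.8. Change-score ratios, by formula: 4.3% to 5.7%.

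**Self-selected v assigned (62 v 63).** Simulated: 5.0% to 5.2% for SD ratios from 0.5 to 2.

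**Welch on the same draws.** At 125 v 31 it gives 4.95% to 5.1% over SD ratios from 0.5 to 2.

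**Price of Welch at equal variances, 125 v 31.** Its df is (1/125 + 1/31)² / [(1/125)²/124 + (1/31)²/30] = 46. The critical value is then 2.013 instead of 1.975, a typical interval width about 1.9% greater.

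**The case against.** The strongest reply is textual. The Statistical Analysis section never says pooled or equal variances, and authors often write Student t test generically. Its opening sentence compares periods with baseline, and the t test sentence names no arm contrast. The 125 v 31 comparison has to be assembled from the allocation ratio, the number randomized and the Sample Size section. This stands as a limit on certainty: the equal-variance form and the between-arm use are both readings. They are the ordinary readings, since the objectives and Sample Size name contrasts between arms. If the t test were purely before-after within an arm, the 4:1 imbalance would not enter, but the arms would then have no unadjusted comparison and the sentence would still need rewording.

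A reader might also infer that the control contrast carries a type I error of 8.6% or more. The documents do not support that. They give no SDs. The ratio of 1.25 comes from a cut that works, so the null is false there and 8.6% is non-coverage of a nominal 95% interval (about 91.4% actual coverage). The same holds for the change-score ratios derived from that cut. Change from baseline is also the quantity the section describes, and on that scale the mechanism gives only about 4% to 6%. The proportional-cut argument does not carry over to GAD-7, PHQ-9 or mood.

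Finally, the adjusted regressions do not use this test. If their within-participant error structure is implemented with cluster-robust standard errors, unequal variances are allowed for there.

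**Conclusion.** The point holds in a limited form. The named test, read in its usual equal-variance form, can be miscalibrated for unadjusted contrasts with control because those contrasts are about 4:1 pooled or 2:1 per arm. At 125 v 31 the two-sided rate is about 6% for a control/intervention SD ratio of 1.07, 8.6% for 1.25 and 2.5% for 0.8. These figures rest on assumed SD ratios, normal data and group sizes derived from 156 at 1:2:2. If the variances are equal there is no error.

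It would go too far to say that the unadjusted p-values are wrong, or that the trial's conclusions depend on this. Self-selected v assigned is near 1:1 and is not exposed, and the adjusted analyses are outside the point. It is a minor improvement that is nearly free to make.

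**What to change.** In Statistical Analysis, replace the Student t test with the Welch (unequal-variance) t test for each unadjusted between-arm comparison. Apply it to one summary value per participant, such as mean change from baseline in the period concerned, and report the difference with its Welch confidence interval. State the arm contrasts in the same sentence so that the test is tied to them.

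The cost is a short wording change and one software option in Stata or R. When variances are equal there is no meaningful loss.

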#### Preregistration

Over 2 weeks, we conducted preregistration to gather expressions of interest. A total of 327 individuals expressed interest in the study. The individuals who displayed interest in the study were requested to complete the baseline survey, which included information regarding demographics, daily mobile phone time, past attempts to reduce screen time, willingness to reduce screen time, and GAD-7 and PHQ-9 for assessing anxiety and depression (a list of collected data is summarized in Table 1). Participants were also asked to report their daily mobile screen time and upload screenshots of the digital well-being app for the week before preregistration.

The digital well-being tools offer a daily overview of a person’s phone use: the number of times the user checks their phone and the screen time. The screen time measures the total and app-wise time of the phone use. Participants share their mobile screen time through a weekly survey asking them to fill in the total time in hours and minutes of screen time for each day as displayed in the digital well-being app. As proof, the participants were asked to upload a screenshot of the digital well-being app for that week. A screenshot of the digital well-being app is shown in Figure 3. The study team checks whether the screen time in the survey matched with the screenshot. The study team provided step-by-step visual instructions for the process of uploading the screenshot from the digital well-being app. Of the 327 individuals interested in the study, 207 provided consent and completed the baseline survey.

**Table 1 table1:** Data collection at various stages of the study.

Data category	Expression of interest	Baseline^a,b^	End of intervention^a,b^	End of postintervention^a,b^
Basic information and contact details	✓	✓	✓	✓
Demographic		✓		
Information on willingness, difficulty, and magnitude in reducing mobile screentime		✓		
Information about mobile use		✓		✓
Phone addiction scale	✓	✓		✓
Generalized Anxiety Disorder–7		✓	✓	✓
Patient Health Questionnaire–9		✓	✓	✓

^a^Daily mobile screen time use: participants share their daily screen time and upload screenshots of their screen time by using the digital well-being feature on their Android mobile phones through self-administered weekly surveys.

^b^Daily mood survey: mood data are collected daily through WhatsApp messages, using a 1-10 scale that is sent at varied times of the day.

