#### Baseline (Mobile Screen Time)

The 2-week period following the preregistration was the baseline period. Every Sunday during this period, we emailed participants who had completed the baseline survey. They were instructed to provide their daily mobile screen time for the preceding week and upload a screenshot of the digital well-being app on their phones. Two reminder emails were sent to those who did not respond. Additionally, participants received a daily mood survey via WhatsApp (Meta) every day. Throughout the 2-week baseline period, 156 participants shared their mobile screen time for at least 1 week, while those who did not respond were excluded from the study.

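### The adjusted GAD-7, PHQ-9 and mood models list only age, gender and status as covariates; adding the participant's own baseline score would gain precision and remove dependence on chance baseline imbalance

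*Protocol article*

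**What the plan says.** The Statistical Analysis section covers GAD-7, PHQ-9 and daily mood together with screen time and target achievement. Effects are obtained "by comparing variables of interest between the intervention and baseline and between the postintervention and baseline periods". For the adjusted effects, "we will use simple ordinary least square regression adjusting for participant-level covariates: age, gender, and employee or student", with a separate equation for each dependent variable. On the errors: "We assume errors to be correlated within each participant but uncorrelated across participants". A model that uses the baseline explicitly is named for one outcome: "For mobile screen time, we will estimate a difference-in-difference ordinary least square regression". For the rest, "The regression equations are provided in Multimedia Appendix 1", and that appendix is not shown.

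The baseline values exist. The Preregistration section lists "GAD-7 and PHQ-9 for assessing anxiety and depression" in the baseline survey, and Table 1 marks both at baseline. In the two baseline weeks, "participants received a daily mood survey via WhatsApp (Meta) every day". On the design side, "The allocation was stratified based on 2 variables: status in the institute (employee or student) and the quartile of baseline average mobile screen time".

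**The concern.** A participant's earlier score on the same scale usually predicts the later score better than age, gender or occupation does. Here it is available before allocation for all three mental health outcomes, yet it is not among the listed covariates. Stratification covers status and screen time, so nothing in the design balances the arms on anxiety, depression or mood.

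The third objective rests on these outcomes. The trial randomized 156 against a target of 300, which leaves about 31 controls at 1:2:2, and the Limitations section concedes that power may be insufficient. Precision that can be recovered from data already in hand is worth having. With arms of this size, the result should also not depend on which arm happened to start with the higher scores.

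**Working it through.** **Inputs from the protocol article.** 156 randomized at 1:2:2, so about 31 control, 62 self-selected and 62 assigned; the two intervention arms together are about 125. Alpha .05 and 80% power (Sample Size); two-sided, from the t test in Statistical Analysis.

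**Assumed.** The baseline to follow-up correlation r is not given, so r = 0.4 to 0.8 is used as a range. Further assumptions are equal SDs at baseline and follow-up, and complete follow-up of all 156.

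The plan states no precision figure for the mental health outcomes, so there is none to reproduce. The Sample Size section gives effects of 0.12 and 0.15 but names no outcome, so they are not used as a yardstick here.

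**Variance under each reading.** Work in units of the follow-up variance and subtract b times the baseline score from the follow-up score. The variance is then 1 − 2br + b².
- Follow-up only (b = 0): 1
- Change score, or difference-in-difference with arm-by-period terms (b = 1): 2(1 − r)
- Baseline score as covariate (b = r, the minimizing value): 1 − r²

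The covariate model is never worse for r from 0 to 1, because 1 − (1 − r²) = r² ≥ 0 and 2(1 − r) − (1 − r²) = (1 − r)² ≥ 0. Estimating b costs one degree of freedom, which is negligible here.

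| r | Change 2(1 − r) | Covariate 1 − r² | Less variance than change | Less variance than follow-up only |
|---|---|---|---|---|
| 0.4 | 1.20 | 0.84 | 30% | 16% |
| 0.5 | 1.00 | 0.75 | 25% | 25% |
| 0.6 | 0.80 | 0.64 | 20% | 36% |
| 0.7 | 0.60 | 0.51 | 15% | 49% |
| 0.8 | 0.40 | 0.36 | 10% | 64% |

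**Detectable difference**, 125 v 31: 2.80 × √((1/125 + 1/31) × factor), where √(1/125 + 1/31) = 0.20.
- r = 0.6, change score: 2.80 × 0.2006 × √0.80 = 0.50 SD
- r = 0.6, covariate: 2.80 × 0.2006 × √0.64 = 0.45 SD
- r = 0.6, follow-up only: 2.80 × 0.2006 = 0.56 SD
- Change score to covariate at the ends of the range: 0.62 to 0.51 SD at r = 0.4, and 0.36 to 0.34 SD at r = 0.8
- Self-selected v assigned (62 v 62), r = 0.6: 0.45 SD with change score, 0.40 SD with the covariate

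At r = 0.6, the gain over a change score equals that from analysing 156 × 0.80/0.64 = 195 participants.

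**Chance imbalance.** The baseline difference between 125 and 31 has an SD of about 0.20. For a baseline difference δ, the expected shift in the estimate is rδ for follow-up only, −(1 − r)δ for a change score and 0 with the covariate. At r = 0.6 and δ = 0.20, the shifts are 0.12, −0.08 and 0 SD.

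A simulation (4,000 runs per correlation; arms of 62, 62 and 32; self-selected v assigned) agrees. At r = 0.3, 0.5, 0.7 and 0.8, the correlation of the estimate with the baseline imbalance was −0.59, −0.49, −0.38 and −0.28 for difference-in-difference. It was +0.31, +0.48, +0.70 and +0.81 for follow-up only, and between −0.01 and +0.04 with the covariate.

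**The listed covariates.** In a stacked difference-in-difference with complete data, age, gender and status do not vary over time, so as additive terms they drop out of the arm-by-period estimate. Under that reading, the listed adjustment adds essentially nothing.

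**The case against.** A reader might infer that the mental health analyses ignore the baseline score altogether. The text does not support that. The section opens by comparing each period with baseline for these very outcomes. The within-participant error assumption also implies several records per participant, although two follow-up surveys or daily mood ratings would imply that too. With the equations in an unseen appendix, the listed covariates cannot be taken as the full right-hand side of every model. It follows that the largest figures, the 16% to 64% gain and the move from 0.56 to 0.45 SD, belong to the reading the text supports least.

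A reader might also infer bias. Change-score and follow-up-only estimates are both unbiased on average under randomization; the shifts above are conditional on the imbalance that happens to occur. The smallest gain over a change score comes at high correlation, which is plausible for mood averaged over many days. Setting the shifts against the planning effects of 0.12 and 0.15 would be a mismatch, because those effects are not tied to mental health.

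Finally, the third objective asks about screen time reduction, and a multilevel model of mood on screen time is also planned. A baseline covariate improves the between-arm effect only, and it cannot simply be added to a model in which baseline rows are stacked as outcomes.

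All of this stands and limits the size of the point. It does not remove it: the baseline covariate is at least as precise under each reading, so the recommendation does not depend on the appendix.

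**Conclusion.** The point holds as a moderate, nearly free improvement. The article lists three covariates and no baseline score for GAD-7, PHQ-9 and mood, uses the baseline only as the comparison period, and names a baseline-using model only for screen time. Against the better-supported change-score or difference-in-difference reading, the covariate lowers variance by 30% to 10% for r from 0.4 to 0.8. The gain reaches 16% to 64% only if the models turn out to be follow-up only. The detectable-difference figures rest on the assumed correlation, equal SDs, complete follow-up and, for 125 v 31, a pooled intervention v control contrast that the section does not itself spell out for these outcomes.

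**What to change.** State in Statistical Analysis and in the appendix equations how the baseline enters the mental health models. For the between-arm adjusted effect:
- Regress GAD-7 at end of intervention, and at end of postintervention, on arm, baseline GAD-7, age, gender and status. Take the arm coefficient as the effect.
- Do the same for PHQ-9 with baseline PHQ-9.
- For mood in each period, use the participant's mean mood over the baseline weeks as the baseline covariate.
- Use follow-up records only as the dependent variable, without stacking baseline rows as outcomes.
- For participants with no baseline mood reply, use a missing indicator or mean imputation so that no randomized participant is dropped. This missingness precedes allocation, so it cannot depend on arm.

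The cost is one covariate per model and, if the equations now stack the periods, a minor restructuring. No new measurement is needed. The abstract puts the end of data collection in November 2023, so a change made after that should be labelled as such, with the originally specified analysis reported beside it.

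### Baseline screen time was a stratifier but is not a covariate: the planned difference-in-difference is unbiased, but its standard errors are about 3–15% wider than ANCOVA would report

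*Protocol article*

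**What the plan says.** Under Randomization and Blinding, allocation is "stratified based on 2 variables: status in the institute (employee or student) and the quartile of baseline average mobile screen time", in permuted blocks of 5 at 1:2:2.

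Under Statistical Analysis, unadjusted effects are differences in means with a two-sided t test. Adjusted effects come from ordinary least squares "adjusting for participant-level covariates: age, gender, and employee or student". The main outcome has its own model: "For mobile screen time, we will estimate a difference-in-difference ordinary least square regression", with dummy variables for period. On the error structure: "We assume errors to be correlated within each participant but uncorrelated across participants". The formulas themselves are elsewhere: "The regression equations are provided in Multimedia Appendix 1". That appendix is not among the documents reviewed.

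The article does not mention ANCOVA, a baseline covariate or terms for the strata.

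**The concern.** Of the two stratification factors, the covariate list keeps employee/student status and drops baseline screen time. The dropped factor is the baseline of the main outcome, so it is likely to be the stronger predictor.

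Two things follow for screen time. First, stratifying on a prognostic factor reduces the true sampling variation of the arm comparison. A model that does not use the factor reports a standard error that misses this reduction. Second, differencing is the best use of baseline only if the true slope of follow-up on baseline is 1. In a randomized trial ANCOVA estimates that slope, and apart from one degree of freedom it cannot do worse.

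Precision is at stake, in a trial that randomized 156 against a target of 300 and whose Limitations section already concedes possible lack of power.

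**Working it through.** **Inputs from the article.** 156 randomized at 1:2:2, so about 31.2 control and 62.4 in each intervention arm. There are 2 × 4 = 8 strata and blocks of 5. Tests are two-sided with alpha .05. Effects are d = 0.12 (self-selected v assigned) and d = 0.15 (intervention v control). **Assumed:** rho, the correlation between a participant's baseline and follow-up means, from 0.5 to 0.9, with equal SDs.

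**The plan's own figure.** The article states no precision for this analysis, only the target of 300. As a plain comparison of means that target does not reproduce: d = 0.12 needs 1,091 per arm. With 120 per arm, 80% power would require a variance factor of about 0.110. For a change score that means 2(1 − rho) = 0.110, so rho ≈ 0.945. The article states no such value, so it cannot serve as an input. The sample size is a separate matter.

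**Step 1: the listed covariates.** Age, gender and status do not vary over time. As main effects in a balanced panel they cancel from the within-person change, so the arm-by-period coefficient is the same with or without them. A main effect of baseline quartile would cancel too. For screen time, the missing stratifier is therefore the same issue as the choice between DiD and ANCOVA.

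**Step 2: variance.** Let s0 and s1 be the baseline and follow-up SDs.
- DiD: s0² + s1² − 2·rho·s0·s1
- ANCOVA: s1²(1 − rho²)
- Difference: (s0 − rho·s1)², which is never negative

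With equal SDs these are 2(1 − rho) and 1 − rho², so the ratio of standard errors is √[2/(1 + rho)]. The 95% half-width for self-selected v assigned is 1.96 × √(2/62.4 × variance factor), in SD units.

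| rho | SE ratio DiD/ANCOVA | Half-width DiD → ANCOVA | Power at d = 0.12, DiD → ANCOVA |
|---|---|---|---|
| 0.5 | 1.155 | 0.351 → 0.304 | 9.9% → 11.8% |
| 0.7 | 1.085 | 0.272 → 0.251 | 13.7% → 15.4% |
| 0.8 | 1.054 | 0.222 → 0.211 | 18.4% → 20.0% |
| 0.9 | 1.026 | 0.157 → 0.153 | 32.2% → 33.6% |

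For pooled intervention v control at d = 0.15, power goes from 11.3% to 13.7%, 16.0% to 18.1%, 21.9% to 23.9% and 38.8% to 40.5%.

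**Step 3: calibration under the stratified design.** This was simulated with 3,000 runs per rho, self-selected v assigned. DiD was run as a regression of the change score on arm and status.

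| rho | DiD mean SE / true SD | DiD type I | ANCOVA mean SE / true SD | ANCOVA type I |
|---|---|---|---|---|
| 0.5 | 0.179 / 0.159 | 2.9% | 0.155 / 0.155 | 5.4% |
| 0.7 | 0.139 / 0.133 | 3.9% | 0.128 / 0.131 | 5.5% |
| 0.8 | 0.113 / 0.109 | 4.1% | 0.107 / 0.108 | 5.3% |
| 0.9 | 0.080 / 0.076 | 4.0% | 0.078 / 0.076 | 4.2% |

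Pooled intervention v control, with DiD and 3,000 runs, gave 0.200 / 0.179 (2.5%) at rho 0.5, 0.155 / 0.146 (3.7%) at 0.7 and 0.089 / 0.088 (4.5%) at 0.9. The Monte Carlo error of a 5% rate is √(0.05 × 0.95/3,000) ≈ 0.4 points, so at rho 0.9 the shortfall is barely distinguishable from none.

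The true SDs of the two estimators are close (0.159 v 0.155 at rho 0.5). Most of the gap in Step 2 is thus a reported standard error that ignores the stratification. Adding quartile to the change-score regression recovers most of it: the mean SE at rho 0.5 falls from 0.179 to 0.158.

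**Step 4: which rho is plausible.** Let s be the stability of a person's true level, and ICC the share of daily variance that lies between people. For a baseline mean of n0 days and a follow-up mean of 35 days, rho = s·ICC / √{[ICC + (1 − ICC)/n0]·[ICC + (1 − ICC)/35]}. With ICC 0.3–0.7, s 0.7–1 and n0 of 7 or 14, all assumed, rho runs from 0.59 to 0.98. The 15% figure is therefore at the unfavourable end.

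**The case against.** **The equations are in an appendix not seen here.** They could contain a baseline or stratum term. That limits certainty, but the article's text names a specific covariate list without one, and the appendix cannot be presumed to contradict it.

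**DiD already uses baseline screen time.** This is correct. A reader might infer from the covariate list that baseline is ignored, or that screen time is compared on follow-up values alone with a far more conservative test. The documents do not support that: baseline enters as the pre-period outcome, and differencing removes most between-person variation when rho is high.

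**The error is on the safe side.** This is also correct. A reader might infer a biased or invalid analysis, but the estimator is unbiased under randomization, and the type I error is below 5%, not above it.

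**The power gain is small.** This stands. Larger gains appear only if one assumes an effect well above the article's own 0.12 and 0.15.

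**Changing a preregistered analysis late has a cost.** This stands too. The abstract says data collection concluded in November 2023, and the research team knew the allocation. It affects how the change is made and labelled, and does not remove the case for it.

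**Conclusion.** The point holds as one of efficiency and calibration. The design stratifies on baseline screen time. The stated model neither includes it as a covariate nor gains from the covariates it does list for the screen-time DiD. For rho from 0.5 to 0.9, reported standard errors are about 15% to 3% wider than under ANCOVA, and type I error is about 2.5–4.5%. These figures rest on an assumed rho, equal SDs over time, all 156 participants contributing, and the unseen equations matching the text. With missing weeks the panel is unbalanced and the listed covariates would alter the estimate slightly. A reader might infer that the change would rescue the trial's power. It would not: at d = 0.12 the gain is 1–2 points, and power stays below 35% throughout the range.

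**What to change.** For the intervention and postintervention periods separately, regress mean daily screen time (or daily values with participant-clustered errors) on arm, continuous baseline mean screen time, employee/student status, age and gender. Baseline quartile may be added. Report DiD alongside.

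For GAD-7, PHQ-9 and mood, adjust for that outcome's own baseline value, which Table 1 shows is collected. Baseline screen time is not the useful term there: the Introduction cites a study in which digital media use explained at most 0.4% of the variation in adolescent well-being.

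No new data are needed for screen time, since every randomized participant supplied at least one baseline week. The cost is to credibility, because the trial is preregistered and data collection has ended. Fix and date the change before any outcome is examined by arm. If that is no longer possible, label ANCOVA post hoc and keep DiD as the planned analysis.
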